## Abstract

**Background**: Young children with spinal muscular atrophy type 1 (SMA1) have limited independent mobility and participation that may lead to cognitive development delays. Implementing early powered mobility in interventions may help them to learn self-initiated movement, play, and having fun to participate in natural settings. The aim of this study is to evaluate the effectiveness of an early power mobility intervention for increasing participation, functional ability, and quality of life in young children with SMA1. **Methods**: AMEsobreRuedas is a randomized waiting list controlled clinical trial. A sample of 24 children (10 months-5 years old, with SMA1) will be randomly allocated to two groups. The experimental group will perform a family-centered intervention with powered mobility for 16 weeks in their natural environment: a 12-week-structured program three times a week; and a 4-week follow-up with free use of the powered mobility device. The control group (waiting list) will keep their routine and will receive the same intervention after the experimental group. Five assessments will be carried out at baseline and weeks 4, 8, 12, and 16. Primary outcomes are participation (YC-PEM); functional ability (PEDI-CAT); and quality of life (PedsQL-Neuromuscular module). **Results**: It is expected that this study will provide further knowledge about the positive impact of powered mobility for the analyzed variables. Moreover, family engagement in the intervention and establishment of functional goals may help to add valuable information about real needs in future research. **Conclusions**: Early powered mobility could increase the opportunities for children with SMA1 to learn to move independently and participate in their natural environment.

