### 2.1. Study Sample

Children with SMA1, between 10 months and 5 years old, who have no prior experience with powered mobility interventions or have used a powered mobility device for less than 7 h in the month preceding this study will be included. Exclusion criteria are children with severe visual impairments, a body weight exceeding 25 kg—MROC requirement, those who use a respirator, or those with other health conditions affecting the neuromusculoskeletal system that may interfere with the use of powered mobility [26,29].

Sample size calculation was performed using G*Power version 3.1.9.4. The calculation was based on the following parameters: an alpha (α) level of 0.05, which corresponds to a 5% chance of a type I error (incorrectly rejecting the null hypothesis when it is true); a statistical power (1-β) of 0.80, which means there is an 80% chance of correctly rejecting the null hypothesis if there is a true effect; and a medium effect size of 0.5 due to the lack of previous studies in this population and the use of powered mobility. Based on these parameters, the calculation determined that 26 participants, with 13 participants in each group, would be needed to achieve adequate statistical power for this study. To account for a potential dropout rate of 20%, a total of 32 participants will be recruited (*n* = 16 for each group) to ensure that the final sample size remains sufficient for analysis.

Recruitment will be performed at early care centers in collaboration with the Spanish Spinal Muscular Atrophy Foundation (*FUNDAME: Fundación de Atrofia Muscular Espinal*). An informational session will be held with the families of potential participants to explain the aims and procedures of this study.

Once families have shown their desire to participate and signed the informed consent forms, a member of the research team—not involved with assessments or interventions—will randomly assign the participants to two groups: the experimental group and the control group (waiting list group).

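### The Abstract randomises 24 children, but Section 2.1 recruits 32 and needs 26 for analysis, so 24 misses the plan's own minimum even with no dropout

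*Protocol article*

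**What the plan says.** The Abstract gives a single number with no derivation: "A sample of 24 children (10 months-5 years old, with SMA1) will be randomly allocated to two groups".

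Section 2.1 (Study Sample) gives a calculation made in G*Power. Its inputs are "an alpha (α) level of 0.05, which corresponds to a 5% chance of a type I error", "a statistical power (1-β) of 0.80" and "a medium effect size of 0.5 due to the lack of previous studies in this population". From these, "the calculation determined that 26 participants, with 13 participants in each group, would be needed to achieve adequate statistical power". The next step is the dropout allowance: "To account for a potential dropout rate of 20%, a total of 32 participants will be recruited", stated as 16 per group, with the purpose that enough children remain for the analysis.

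Section 2.1 does not say which test was used, whether it was one- or two-sided, or whether 0.5 is a standardised mean difference or an ANOVA effect size. Nowhere does the article explain the 24 or describe it as a revised target, a number enrolled so far, or an expected number of completers.

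**The concern.** The Abstract and Section 2.1 both say, in the future tense, how many children will enter the two randomised groups, and they give different numbers. A full protocol held elsewhere could show which number is intended, but it could not make both right.

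The smaller number also fails the requirement that the article sets for itself. A trial that randomised 24 children could not reach 26 analysed even if every child completed.

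What is at stake is how enrolment will be judged. With two published targets, a trial that stops at 24 could be reported as fully enrolled (by the Abstract) or as 25% short (by Section 2.1: 8/32 = 0.25). In a disease as rare as the Introduction describes, that situation could well arise, and it should be settled before results are known.

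**Working it through.** **Inputs**
- Number randomised: 24 (Abstract).
- Analysable number needed: 26, 13 per group (Section 2.1).
- Dropout: 20% (Section 2.1).
- Number recruited: 32, 16 per group (Section 2.1).
- Alpha 0.05, power 0.80, effect size 0.5 (Section 2.1).

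**Step 1. Does 32 follow from 26?**
- Multiplying up: 26 × (1 + 0.20) = 31.2, rounded up to 32. This matches the stated figure.
- Dividing by the retention rate: 26 / (1 − 0.20) = 32.5, rounded up to 33, or 34 for equal groups.

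The stated 32 is reproduced by the first formula and is within two children of the second. The 26 and the 32 therefore belong together.

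**Step 2. Can 24 be reconciled with them?**
- As the recruitment target: 32 − 24 = 8 children fewer, 25% of 32.
- As the analysable minimum: 26 − 24 = 2 children fewer.
- As the completers out of 32: 32 × 0.8 = 25.6, not 24.

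None of these readings yields 24.

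**Step 3. What 24 leaves after the planned dropout**
- 24 × 0.8 = 19.2, about 19 children.
- 26 − 19 = 7 short; 7/26 = 27% (or 6.8/26 = 26% without rounding).

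**Step 4. What this costs in power (assumption-dependent)**

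One set of inputs that reproduces 26 exactly is a repeated-measures ANOVA, between-factors test, with f = 0.5, two groups, m = 2 measures and correlation ρ = 0.5 between measures. The test family, m, ρ and the reading of 0.5 as f are assumptions; the article does not state them. The noncentrality parameter is

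λ = f² × N × m / (1 + (m − 1)ρ) = 0.25 × N × 2 / 1.5 = N / 3,

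with 1 and N − 2 degrees of freedom. Power from the noncentral F distribution at alpha 0.05:

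| Analysed N | λ | Power |
|---|---|---|
| 26 (Section 2.1) | 8.67 | 0.806 |
| 24 (Abstract, no dropout) | 8.00 | 0.771 |
| 19 (Abstract, 20% dropout) | 6.33 | 0.660 |

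On this model, 24 with no dropout costs about 3.5 percentage points (0.806 − 0.771), and 24 with the planned dropout costs about 15 (0.806 − 0.660).

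**Range.** A one-sided paired t-test with d = 0.5 needs 27, also close to 26; its power is 0.798 at 26 and 0.768 at 24, so the cost of having 24 is about the same. A two-sided comparison of two independent groups with d = 0.5 needs 64 per group and does not reproduce 26.

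**The case against.** The strongest reply is that Section 2.1 is the operative text. It gives parameters, per-group numbers and a dropout allowance, while the Abstract gives a bare number. An Abstract left unrevised is a plausible explanation, in which case one number changes and the design and power are untouched. Nothing in the article shows that an allocation list or a recruitment stop has used 24. All of this stands as a limit on the consequence. It does not remove the contradiction, because the article does not confirm that explanation.

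Three stronger readings are tempting and are not supported.

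- **That the article gives three incompatible sizes.** It does not. The 26 is the number to analyse and the 32 the number to recruit; only the 24 conflicts.
- **That 32 is itself a material error because it should be 33 or 34.** Dividing by 0.8 is the more exact inflation, and 32 leaves an expected 25.6 completers, 0.4 of a child under 26. Under the model in the working, power is 0.789 at 25 and 0.806 at 26, a difference of about 2 points. This merits a side note only.
- **That power falls to between 17% and 23%.** Those figures (0.170 at 9 per group, 0.185 at 10, 0.232 at 13) are correct for a two-sided independent t-test with d = 0.5. Section 2.1 does not state that test, and it does not reproduce 26. Whether 26 is well founded is a separate question and is not evidence on the mismatch between 24 and 32.

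**Conclusion.** The concern holds in this form: the Abstract's 24 contradicts the 32 in Section 2.1 and is below the stated minimum of 26 before any dropout. This rests on the article's own numbers and needs no modelling assumption. The shortfall is 8 children against the recruitment target, 2 against the analysable minimum with full retention, and about 7 after the planned 20% loss.

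The power cost does depend on assumptions. Under the between-factors ANOVA inputs that reproduce 26, power falls to about 0.77 with 24 analysed and 0.66 with 19. If 32 is the true target, none of this loss arises and the error is confined to the Abstract. It still must be corrected, because the target sample size is stated in two conflicting ways and one of them fails the plan's own requirement.

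**What to change.** State one recruitment target in both the Abstract and Section 2.1.

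- **If the target is 32:** change the number in the Abstract. Nothing else is needed. Optionally, note in Section 2.1 that 20% dropout from 32 leaves an expected 25.6 completers, marginally under 26.
- **If the target is 24:** revise the sample-size paragraph in Section 2.1 to give the power or the detectable effect for about 19 to 24 analysed children, with the test and inputs named, and remove the statement that the final sample will remain sufficient.

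The cost is a text correction. It requires no extra recruitment and no change to the analysis, and it should be made before results are known.

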## 1. Introduction

Spinal muscular atrophy (SMA) is an autosomal recessive genetic disorder due to progressive muscle weakness and atrophy. It has an estimated incidence of 1 in 11,000 live births [1]. Children with SMA exhibit a wide spectrum of symptoms with a severity clinically classified from type 0 to 4 (from highest to lowest severity), based on the highest motor milestone achieved [1,2]. Traditionally, SMA classification has been based on the age of symptom onset. However, advances in therapeutic options—such as nusinersen, zolgensma, and risdiplam—along with the possibility of early administration, have been showing the potential to substantially transform the clinical overview. These treatments can increase the levels of the survival motor neuron (SMN) protein, slowing disease progression and improving outcomes [3,4]. According to the consensus statement for standard care in SMA [5], updated in 2018 [6,7] and revised in 2024 [8], the age of symptom onset remains a crucial factor for newly diagnosed infants and those identified through newborn screening. Since motor function and weakness may vary across the musculoskeletal system in young children with SMA, evaluating developmental and motor function prior to treatment is essential. Additionally, proactive rehabilitation should be emphasized to optimize developmental outcomes [8,9]. 

Children diagnosed with SMA type 1 (SMA1) usually present proximal weakness, hypotonia, areflexia, and feeding difficulties within the first 6 months of age. These symptoms lead to delays in motor milestones and significant challenges in achieving independent sitting or walking [10]. Despite these difficulties, recently, the inclusion of disease-modifying therapies has been demonstrating improvements in survival rates and functional capabilities in children with SMA1 [11].

For young children with severe mobility limitations, such as those with SMA1, there can be considerable restrictions in participation and reduced social interaction with caregivers and peers. These limitations often result from the poor self-initiated mobility and delays in learning how to move and cognitive development [12,13]. Dunaway et al. [14] point out that there is a critical therapeutic window for mobility development, suggesting that strategies focused on self-initiated movement can profoundly impact behavior, self-esteem, and social participation. Ideally, providing independent mobility should occur around between 7 and 12 months, as close as possible to the typical ages for crawling and walking, to help minimize delays in cognitive development and facilitate more effective social and motor development [14]. Powered mobility devices offer a means for self-initiated movement and environmental exploration [15]. It is also associated with benefits that extend beyond mobility, potentially improving social skills [14,15,16], communication, cognitive development, and peer interactions [17,18].

Therefore, children with SMA1 are likely to benefit from the early introduction of powered mobility as a valuable strategy intervention for moving, playing, and engaging with their natural environment [17,19]. This approach represents a significant shift in how we support children with SMA, potentially expanding their world and fostering greater social interaction and independence [19,20,21].

A systematic review conducted by Hospodar et al. [20] evaluated the use of modified ride-on cars (MROCs) for children with mobility limitations. The review found that children as young as 7 months could engage with these toys, which enhanced their activity levels and participation. Additionally, MROCs positively impacted family-related outcomes. MROCs are engaging toys that can encourage interaction between infants with mobility limitations and their peers, thereby enhancing social participation [22,23,24]. Positive effects were observed in terms of enjoyment during powered mobility interventions and improved social skills, including better interaction with peers in playgrounds and in playgroups [17,18,20].

Nevertheless, while powered mobility offers numerous functional and developmental benefits, simply incorporating an MROC into a child’s routine is not sufficient. Children also require opportunities to practice in suitable settings to ensure successful learning and integration [21,25,26]. At present, there is a lack of consensus regarding recommendations for interventions that include early powered mobility in terms of intensity, duration, and implementation for children with SMA1, since the evidence remains unclear [21].

Therefore, the aim of this randomized clinical trial (RCT) is to prove the effectiveness of an early powered mobility intervention for enhancing participation, functional ability, and quality of life in young children diagnosed with SMA1. As secondary aims, the impact of the intervention on the level of learning of powered mobility, functional goals, parental stress, and satisfaction with the intervention and with the use of MROC will also be considered.

## 2. Materials and Methods

A single-blinded waiting list RCT will be conducted. This study adheres to ethical principles outlined in the Declaration of Helsinki [27] and the Spanish Law on Personal Data Protection and Guarantee of Digital Rights [28]. It has been approved by the Ethics Committee of the University Hospital in Toledo (Ref No. 842) and is registered on www.clinicaltrials.org (accessed on 18 October 2022) with the ID: NCT05589987.

### 2.1. Study Sample

Children with SMA1, between 10 months and 5 years old, who have no prior experience with powered mobility interventions or have used a powered mobility device for less than 7 h in the month preceding this study will be included. Exclusion criteria are children with severe visual impairments, a body weight exceeding 25 kg—MROC requirement, those who use a respirator, or those with other health conditions affecting the neuromusculoskeletal system that may interfere with the use of powered mobility [26,29].

Sample size calculation was performed using G*Power version 3.1.9.4. The calculation was based on the following parameters: an alpha (α) level of 0.05, which corresponds to a 5% chance of a type I error (incorrectly rejecting the null hypothesis when it is true); a statistical power (1-β) of 0.80, which means there is an 80% chance of correctly rejecting the null hypothesis if there is a true effect; and a medium effect size of 0.5 due to the lack of previous studies in this population and the use of powered mobility. Based on these parameters, the calculation determined that 26 participants, with 13 participants in each group, would be needed to achieve adequate statistical power for this study. To account for a potential dropout rate of 20%, a total of 32 participants will be recruited (*n* = 16 for each group) to ensure that the final sample size remains sufficient for analysis.

Recruitment will be performed at early care centers in collaboration with the Spanish Spinal Muscular Atrophy Foundation (*FUNDAME: Fundación de Atrofia Muscular Espinal*). An informational session will be held with the families of potential participants to explain the aims and procedures of this study.

Once families have shown their desire to participate and signed the informed consent forms, a member of the research team—not involved with assessments or interventions—will randomly assign the participants to two groups: the experimental group and the control group (waiting list group).

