### 2.8. Statistical Analysis

Quantitative data will be analyzed using SPSS Statistics 22.00 for Windows. Parametric statistical tests will be employed with a significance level set at *p* < 0.05. To compare outcome variables between interventions, the paired Student’s *t*-test will be employed for comparisons involving two measures. For comparisons involving more than two measures, repeated measures ANOVA will be used to identify specific differences between groups or time points. To provide a comprehensive understanding of the results, effect sizes will be calculated for both the *t*-test and ANOVA. Confidence intervals for these effect sizes will also be reported to offer insights into the robustness of the findings.

Photovoice data will be transcribed by the researchers who conducted the online meetings with the families. The transcriptions will be reviewed by an experienced qualitative researcher [48]. Two researchers will independently analyze the data, followed by a group discussion with the research team to develop preliminary results. Thematic analysis will be performed following the principles outlined by Braun and Clarke [49] with support from ATLAS.ti software v.23. Identified themes will be validated by the participating families, who act as co-investigators in this study. This phase, termed “Validation of Analysis by Parents”, allows families to select the themes that best reflect the content of the sentences and photos included in the analysis.

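### Thirteen children per group give about 23% power, not 80%, for a between-group effect of 0.5; 80% is reached only at about 1.15 SD

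*Protocol article*

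**What the plan says.** Section 2.1 (Study Sample) of the protocol article reports a G*Power calculation. The inputs are "an alpha (α) level of 0.05, which corresponds to a 5% chance of a type I error", "a statistical power (1-β) of 0.80" and "a medium effect size of 0.5 due to the lack of previous studies in this population and the use of powered mobility". The conclusion is that "26 participants, with 13 participants in each group, would be needed to achieve adequate statistical power for this study". The number is then raised for losses: "To account for a potential dropout rate of 20%, a total of 32 participants will be recruited", 16 in each group.

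The section does not name the test, the effect-size metric, the sidedness, the number of measurements or a correlation between them. Children are randomised to the intervention or a waiting list, and the Introduction says the aim is to prove effectiveness. Section 2.2 schedules the primary outcomes at baseline and weeks 8, 12 and 16. Section 2.8 plans that "the paired Student’s *t*-test will be employed for comparisons involving two measures", with repeated measures ANOVA for more than two. The Abstract gives a sample of 24 children.

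**The concern.** The label medium attached to 0.5 is the convention for Cohen's d, a difference between group means in SD units. A two-group comparison at d = 0.5 is well known to need more than 60 participants per group, so 13 per group is about a fifth of what those inputs imply.

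The power that matters is the power of the comparison with the waiting list, because only that comparison is protected by randomisation. If that power is far below 80%, a real medium benefit would usually go undetected. The Discussion describes this as, to the authors' knowledge, the first randomised trial of early powered mobility in SMA1, so a null result could be given undue weight.

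**Working it through.** **Inputs.** From section 2.1: alpha 0.05, power 0.80, effect size 0.5, n = 13 per group (16 if nobody is lost). From the Abstract: 24 children, or 12 per group. Assumed, because not stated: two-sided testing (one-sided also tried) and the correlations given below.

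**1. Can the stated 26 be reproduced?** Three settings come near it.

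- *Repeated measures ANOVA, between-groups factor, f = 0.5, m = 2 measurements, correlation r = 0.5.* The noncentrality is λ = N f² m / (1 + (m − 1)r) = 26 × 0.25 × 2 / 1.5 = 8.67 on 1 and 24 degrees of freedom. Power is 0.806, and N = 26 is the smallest even total that reaches 0.80. For two equal groups f = d/2, so f = 0.5 is d = 1.0, a large effect. With the medium value f = 0.25, the same test needs N = 98 with 2 measurements or 82 with 4. Its power at N = 26 is then 0.29 or 0.34.
- *One-sided paired or one-sample t-test, effect 0.5.* This needs 27 children in total (0.798 at 26; 34 if two-sided). It tests change within children and has no control group.
- *Group-by-time interaction, f = 0.25, 4 measurements, r = 0.5.* This gives N = 24 (0.85 at 26). It uses 0.25, not the stated 0.5. If the groups are equal at baseline and differ by d at all three later visits, f = d√3/8, so f = 0.25 means d = 0.25 × 8/√3 = 1.15 SD. With f = 0.5 the interaction test needs far fewer children than 26 (12 with 2 measurements, 8 with 4, at r = 0.5).

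**2. Two independent groups at d = 0.5.** The noncentral t has δ = d√(n/2) and 2n − 2 degrees of freedom. For n = 13, δ = 0.5 × √6.5 = 1.275 on 24 degrees of freedom.

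| Quantity | Two-sided | One-sided |
|---|---|---|
| n per group for 80% power | 64 | 51 |
| Power, 13 per group | 0.232 | 0.342 |
| Effect detectable at 80% power, 13 per group | 1.145 SD | 1.00 SD |

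Two-sided power is 0.278 with 16 per group (detectable effect 1.02 SD) and 0.216 with 12 per group. The required total of 2 × 64 = 128 is about 4.9 times 26.

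**3. Adjusting for baseline.** ANCOVA multiplies the residual variance by 1 − r², so δ = d√(n/2)/√(1 − r²), with one degree of freedom fewer. For 13 per group, two-sided:

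| Assumed r | Power at d = 0.5 | Detectable d at 80% |
|---|---|---|
| 0.5 | 0.29 | 0.99 |
| 0.7 | 0.40 | 0.82 |
| 0.8 | 0.53 | 0.69 |
| 0.9 | 0.80 | 0.50 |

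**4. The group-by-time test with four measurements.** For a true difference of 0.5 SD at each visit after baseline and N = 26, power is 0.22 at r = 0.5, 0.35 at 0.7, 0.50 at 0.8 and 0.82 at 0.9, much the same as ANCOVA.

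**The case against.** The strongest reply is that section 2.1 names no test, and that section 2.8 plans repeated measures ANOVA, not an unadjusted two-sample t-test. Within that family, the between-groups F test with f = 0.5, two measurements and r = 0.5 returns exactly 26 at the stated alpha and power. On that reading the arithmetic is right and only the word medium is wrong. This stands as a plausible account of where 26 came from. It does not rescue the paragraph, because the trial is then powered for 1.0 SD while telling readers it is powered for a medium effect. It also assumes two measurements, where section 2.2 schedules four.

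A second reply is that 1.15 SD applies only without adjustment. That is correct: baseline adjustment or a repeated-measures model lowers the detectable effect. Reaching 80% power at 0.5 SD, however, takes a correlation of about 0.9, which the article does not state and which should not be presumed for parent-reported scales in children aged 10 months to 5 years.

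A third is that SMA1 is rare and a small sample is unavoidable. That is fair, but section 2.1 does not defend 26 on feasibility; it claims adequate power. Nor does the point rest on details a full protocol might supply, because the inputs and the result are both printed and do not agree.

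**Conclusion.** The concern holds. As written, the combination of a medium effect of 0.5, 80% power and 13 per group is wrong for the randomised comparison. Power at d = 0.5 is about 0.23 for an unadjusted two-sided test, so a true effect of that size would be missed about three times in four (1 − 0.232 = 0.768). The effect detectable with 80% power is about 1.15 SD, more than twice the planned one.

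These figures assume a comparison at one time point with 26 children analysed. With baseline adjustment at correlations of 0.5 to 0.7, power is 0.29 to 0.40 and the detectable effect 0.99 to 0.82 SD. Only a correlation near 0.9 would make the stated power true. No setting tried gives 26 for a medium between-group effect without such a correlation. The stated power must be corrected.

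**What to change.** Keep the feasible sample and rewrite the sample-size paragraph in section 2.1 so that it:

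- names the test, effect metric, sidedness and any assumed correlation. A two-sided between-group ANCOVA at week 12 would suit, since section 2.3 has the waiting-list group start the intervention after the 12-week phase;
- states that 26 analysed children give 80% power for a difference of about 1.15 SD unadjusted, or about 0.8 to 1.0 SD with baseline adjustment at a correlation of 0.5 to 0.7, and only about 23% to 40% power at 0.5 SD;
- justifies the number by feasibility in a rare disease;
- says that results will be read as estimates with confidence intervals, and that a non-significant result is not evidence of no effect. Section 2.8 already promises effect sizes with confidence intervals, so this adds only the rule for interpretation.

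The 24 children in the Abstract should be reconciled with the 26 and 32 in section 2.1 at the same time, so that the power statement refers to one sample. The cost is one rewritten paragraph and a less favourable power statement. No extra children are needed.
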